#### Primary Outcome Measure

Assessment of maximal handgrip strength will be performed in accordance with American Society of Hand Therapist guidelines [33]: with the participant sitting comfortably and in an upright position with the elbow of the affected arm close to their body, flexed at a 90° angle, and holding the dynamometer (Jamar hydraulic hand dynamometer, Patterson Medical) in their hand. The other parts of the body are not allowed to move or help to give more strength. The handle position of the dynamometer is adjusted for each participant, so that the middle phalanx of the middle finger is at 90° to the handle. The examiner will provide the participant with standardized verbal instructions. Participants will perform 3 maximal contractions for 5 seconds, while the examiner gently supports the base of the dynamometer. A 60-second-duration rest is taken between each contraction. If the third value is higher than the first and second, a fourth attempt will be added. This will be continued until the last value is lower than the second-to-last value. The mean value of the last 3 attempts will be used as the test score [33].

#### Secondary Outcome Measures

Maximal pinch strength will be assessed with the Baseline Lite Hydraulic Pinch Gauge dynamometer (Fabrication Enterprises). The pinch strength will be measured in 3 configurations—between the index finger and the thumb, the middle finger and the thumb, and the ring finger and the thumb—with the participant sitting in a straight-backed chair without arm supports, the elbow flexed at 90° and close to the body, the forearm in a neutral position, and the wrist in a neutral position or with slight extension (0º-30º) [33]. The pinch gauge is grasped with the distal segment and ventral side of the thumb and finger, while the pinch meter is slightly supported by the examiner. The examiner will provide the participant with standardized verbal instructions. Three maximal isometric contractions will be performed for at least 5 seconds, with a 60-second-duration rest period between each contraction. If the third value is higher than the first and second, a fourth attempt will be added. This will be continued until the last value is lower than the second-to-last value. The mean value of the last 3 attempts will be used as the test score [33].

Static grip endurance is measured in the same way as handgrip strength; however, this test determines endurance during a static hold. Participants will be instructed to squeeze and hold the Jamar hydraulic hand dynamometer with full effort for 30 seconds. Participants will not be informed of the time remaining. Relative endurance for this test was calculated as (*mean force during last second*) / (*mean force during first second*), and larger numbers reflect greater relative endurance (ie, less fatigue) [34].

The Action Research Arm Test is a reliable, valid, and sensitive measurement for dexterity that evaluates 19 tasks for distal and proximal arm motor function and is divided into 4 subscales: grasp, grip, pinch, and gross arm motor function [35,36]. The quality of performance on each item is rated on a 4-point ordinal scale that ranges from 0 (can perform no part of test) to 3 (performs test normally). The maximum score of the Action Research Arm Test is 57 points and will be scored as described in [35].

Jebsen-Taylor Hand Function Test is a reliable and valid test to evaluate functional hand motor skills in different patient groups and healthy people of various ages [37]. The test consists of 7 different unilateral hand skill tasks related to activities of daily living: (1) writing a sentence of 24 characters, (2) turning over 7.6 cm × 12.7 cm cards, (3) picking up and moving small common objects (eg, paper clips, coins, and bottle caps), (4) stacking checkers (test of eye–hand coordination), (5) simulated feeding (eg, teaspoon with beans), (6) picking up large empty cans, and (7) moving weighted (450 g) cans. The duration of each task will be recorded in seconds and summed for the test score [38].

Michigan Hand Outcomes Questionnaire–Dutch Language Version (a total of 57 items) assesses patients’ opinions their hands and health [39,40]. The questions are used to assess out how patients feel and to what extent they are capable of carrying out daily activities in the past week (with the exception of part 3, in which the last 4 weeks is used). The problem is mapped out within 6 domains: total hand function, activities of daily living, work situation, work performance, pain, aesthetics, and satisfaction. Within each domain, items are scored on a 5-point Likert scale. The scores are normalized to a range of 0 to 100. For the pain scale, higher scores indicate more pain. For the other 5 scales, higher scores indicate better performance.

The Motor Activity Log [41] is a semistructured questionnaire that assesses self-perceived amount of use and quality of movement of the affected arm and hand by stroke patients during activities of daily living. This questionnaire consists of 26 activities and has excellent test-retest reliability for both scores of each activity; each activity is rated by the participant for quality of movement and amount of use of the upper extremity on a 5-point scale.

An 11-point numeric pain rating scale—from 0 (no pain) to 10 (the most intense pain imaginable)—is used to measure the subjective intensity of pain (patients select a value that is most in line with the intensity of pain that they have experienced in the last 24 hours). The numeric pain rating scale has good sensitivity, while producing data that can be statistically analyzed [42].

EuroQol 5D-5L (EQ-5D) index is a standardized instrument that is applicable to a wide range of health conditions and treatments [43]. The first part records self-reported problems in mobility, self-care, usual activities, pain and discomfort, and anxiety and depression domains. Each domain is divided into 5 levels of severity, corresponding to no problems, slight problems, moderate problems, severe problems, and extreme problems. The second part comprises a visual analog scale from 0 (worst imaginable health state) to 100 (best imaginable health state). The EQ-5D is designed for self-completion by respondents. In this study, the EQ-5D will be used to calculate a preference-based summary index, based on time trade-off techniques, for which the value 0 represents death and 1 represents perfect health.

Short Form 36 is a 36-item valid and reliable questionnaire to assess the participants’ health perception [44]. The questionnaire consists of multi-item dimensions about the physical and mental well-being of the participant. The total and component scores, physical component summary (average score of the domains physical functioning, physical role functioning, bodily pain and general health), and mental component summary (average score of the domains vitality, emotional role functioning, social functioning and mental health) will be calculated. The will be converted to a scale from 0 to 100, where a higher score indicates a better quality of life [45].

Glove-use data will be automatically recorded by the Carbonhand system, such as total time the system is turned on (hours), average session length (minutes), cumulative number of grasps (for thumb, middle, and ring fingers separately), average frequency of grasps per minute (for thumb, middle, and ring fingers separately) and the average grasp force provided by user (for thumb, middle, and ring fingers). The parameters are extracted from the control unit after the 6 weeks of home use using a USB-connection and dedicated Carbonhand software (version LB.09.07; Bioservo Utility Public) by each participating center.

A diary will be kept daily by the participants during the 6-week intervention period. Participants will be asked to report how often and for how long they use the Carbonhand system each day, when they use the system (morning, afternoon, evening), and during which activities. Information from the diaries will be transcribed by the investigator. The study coordinator will perform thematic analyses on those transcriptions to extract qualitative information about glove use and participants’ experiences using the Carbonhand system.

A semistructured qualitative interview with open-ended questions will be performed by the investigator at the T3 assessment, to collect participants’ experiences about using the Carbonhand system in daily life and the user-friendliness of the system. The interview will last approximately 15 minutes and was developed by Roessingh Research and Development BV in collaboration with Bioservo with the aim of learning about the user experiences and to improve the Carbonhand system. Data extraction (written answers of the interview) will follow the same procedure as that used for the diaries.

If a participant withdraws from the study during the intervention period, we will aim to obtain the reason for stopping, the maximum handgrip strength, and glove-use data and to complete the semistructured interview.

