### Study Procedure

All health care professionals involved in the study received extensive training prior to the start of the patient recruitment in order to standardize the execution of the study across the different centers. Plenary instruction sessions were scheduled; health care professionals were trained in good clinical practice, execution of the study protocol, in fitting and operating the Carbonhand system, and in explaining (following a standard procedure) the use of the Carbonhand system to the participants. All instructions were also documented in logbooks and manuals, which were provided to the professionals. The latest versions of these documents are maintained on a secure project website.

In total, there are 5 assessments for each participant. Three preassessments (T0, T1, and T2) are scheduled across 3 weeks, as baselines, directly prior to the intervention period. After completing the third baseline session, the Carbonhand system is manually adjusted by the professional to the individual participant. Attention is paid to the correct size of the glove and arm straps, the finger length of the glove, and creating 3 support profiles. In addition, instructions about all aspects of the Carbonhand system are given, demonstrated, and practiced with the participant, until the professionals are confident that the participant knows how to use the system properly at home. In addition to receiving the Carbonhand system, all participants will be provided with a short user manual (in Dutch) and an excerpt from the exercise book [30], in which exercises (functional activities that can be used in the home situation) are described for people with almost complete function of the arm.

During the 6-week intervention period, participants use the Carbonhand system at home. Within 1 week of the end of the intervention period, postassessment (T3) is conducted; 4 weeks later, a follow-up assessment (T4) is conducted, to measure the retention of effects.

Monitoring visits by an independent study monitor are planned for each participating center to ensure the continued protection of participants rights and well-being, to assure protocol adherence, and to verify data integrity during the study in compliance with good clinical practice. All protocol deviations will be filed. We anticipate having 5 monitor visits to each center during the course of the study.

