### Outcome Measures

#### Overview

The primary outcome measure of the study is maximal handgrip strength. Secondary outcome measures, related to arm and hand function, functional ability, amount of glove use, pain, and quality of life (Table 1), are only performed on the most affected side. All assessments are estimated to take 1.5 to 2 hours.

During the intervention period, the amount of glove use will be recorded automatically by the Carbonhand system. In addition, participants are asked to keep a diary about daily use of the glove and all activities in which they engage. In order to get a thorough understanding about the experience of the participants of using the Carbonhand system during activities of daily living at home and the user friendliness of the system, semistructured interviews will take place after the intervention period (T3).

**Table 1 table1:** Overview of outcome measures.

Outcome measure	International Classification of Functioning, Disability and Health component	Domain	Assessment
Maximal handgrip strength	Body function	Grip strength	T0-T4
Maximal pinch strength	Body function	Pinch strength	T0-T4
Static grip endurance	Body function	Grip endurance	T0-T4
Action Research Arm Test	Activity	Upper extremity performance	T0-T4
Jebsen-Taylor hand function test	Activity	Fine and gross hand motor skills	T0-T4
Michigan Hand Outcomes Questionnaire–Dutch version	Activity	Self-perceived health state	T0-T4
Motor Activity Log	Activity	Self-perceived upper limb performance	T0-T4
Numeric pain rating scale	Body function	Self-perceived intensity of pain	T0-T4
EuroQol 5 dimension, 5 level	Participation	Self-perceived health-related quality of life	T0-T4
Short-form 36	Participation	Self-perceived quality of life	T0-T4
Glove use data	Activity	Registered amount of use	Intervention period
Diary	Activity	Self-perceived amount of use	Intervention period
Semistructured interview	Activity	Patient’s experiences of Carbonhand use	T3

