### Statistical Analysis

Outcome measures will be analyzed using SPSS statistical software (version 19; IBM Corp). Data from the 3 baseline assessments (T0, T1, and T2) will be averaged (for overall preassessment values). Statistical analysis of the therapeutic effect will be performed on all participants who completed all assessments up to and including T3 and T4. Data from participants who drop out before or during the intervention period will be analyzed separately to analyze the patient characteristics of dropouts, including the reasons for dropout, to identify potentially relevant information regarding reevaluation of target population, device-related issues, to inform proper interpretation of study outcomes.

Normality of data distribution for each outcome measure will be checked by visual inspection and with the Shapiro-Wilks test, prior to analyzing outcome measures. Descriptive statistics will be used for all outcome measures (mean and standard deviation or median and interquartile range as applicable). The overall level of significance will be set to *P*<.05.

In order to assess the effect of the intervention over time, linear mixed models will be used to analyze changes in outcome measures over time. If a significant difference is found between sessions, multiple comparisons are performed with Sidak posthoc analysis. If data are not normally distributed, logarithmic transformation will first be applied to potentially achieve normally distributed data and enable use of linear mixed models for analyses. Otherwise, the Friedman test will be used for nonparametric analysis.

In addition, correlations (Pearson correlation coefficient or the nonparametric Spearman correlation coefficient, depending on data characteristics) between amount of use (measured by diary, Carbonhand system, or Motor Activity Log) or baseline patient characteristics and change in hand function outcome measures will be calculated to evaluate whether an increased dose or specific patient characteristics are associated with better outcomes

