## Results

The study started in June 2019. The first participant was enrolled on June 25, 2019. As of October 2021, we have enrolled 52 participants. As of March 2022, the study is still ongoing due to the COVID-19 pandemic and related restrictions. We expect data collection to be completed in 2022.

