In addition to these strengths, we face some challenges. First, the therapeutic effects of Carbonhand will be assessed using an uncontrolled design because of practical reasons—limited availability of resources in terms of project funding and project duration. Second, some outcome measures, for example those assessed with the Motor Activity Log, Michigan Hand Outcomes Questionnaire–Dutch Language Version, Short Form 36, EQ-5D, and the semistructured interview and diaries, are self-reported, which includes the risk of socially desirable answering. Potential bias is reduced as much as possible by allowing participants to complete the questionnaires by themselves, without interference from the health care professional. Finally, participants that might be disappointed about the effect of the glove may have a higher risk of dropout during or directly after the intervention period. This may influence postintervention (T3) and follow-up (T4) results. In order to prevent this effect as much as possible, professionals were instructed to explain the importance of completing the study to all participants at the start of the study. In addition, the characteristics of the dropout sample will be analyzed to inform proper interpretation of study outcomes. Another limitation is the cumulative collection of glove-use data via the Carbonhand system. This means that the exact amount of use per day per week or per bout of activity cannot be retrieved. In order to obtain insight into day-to-day use of the glove, participants are asked to note this information daily in a diary.

This is the first powered clinical trial to investigate the unique application of an assistive grip-supporting soft robotic glove for use outside of clinical settings with the aim to have a therapeutic effect. Despite the abovementioned challenges, the study will provide a solid knowledge base about the therapeutic effect of 6 weeks of home use of an assistive grip-supporting glove.

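### Participants who withdraw during the glove period are asked for a grip test with no stated time but not for T3 or T4, and the effect analysis then leaves them out

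*Protocol article*

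**What the plan says.** All references are to the protocol article.

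- **Withdrawal rule** (last paragraph of Secondary Outcome Measures). The trigger is "If a participant withdraws from the study during the intervention period". The response is "we will aim to obtain the reason for stopping, the maximum handgrip strength, and glove-use data and to complete the semistructured interview". No time is set for the grip test, and neither T3 nor T4 is mentioned.
- **Schedule** (Study Procedure). "Within 1 week of the end of the intervention period, postassessment (T3) is conducted", and T4 follows 4 weeks later. Table 1 lists handgrip strength, the primary outcome, at T0 to T4.
- **Analysis set** (Statistical Analysis). The therapeutic effect is estimated "on all participants who completed all assessments up to and including T3 and T4".
- **Dropouts** (same section). "Data from participants who drop out before or during the intervention period will be analyzed separately to analyze the patient characteristics of dropouts", together with their reasons for leaving.
- **Acknowledged risk** (Discussion). The authors write that "participants that might be disappointed about the effect of the glove may have a higher risk of dropout" and that this may affect T3 and T4 results. Their remedies are to explain at the outset why completing matters, and to describe the people who drop out.

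**The concern.** The withdrawal rule assumes that some people who leave can still be measured, since it asks them for a maximal grip test and an interview. Yet it does not ask them for the two visits that would give a usable primary outcome. The grip value it does seek has no stated place on the T0 to T4 schedule, and under the Statistical Analysis section it plays no part in the effect estimate.

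The two sections act together. One does not seek the data that would qualify a withdrawer for the analysis; the other leaves out anyone without those data. Because the trial is uncontrolled, no second arm has similar losses that could partly offset the selection, so any difference between completers and withdrawers goes straight into the pre-post change. If people who gain little are more likely to leave, the reported gain is too large.

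The analysis set is also defined by attendance, not by glove use. A participant who hardly wears the glove but attends every visit counts; one who withdraws but could have been measured does not.

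**Working it through.** **Inputs from the Sample Size section:** expected improvement 2.16 kg, SD 5.2 kg, 56 participants needed, 63 after allowing for 10% dropout.

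**The plan's own figures.** 56/0.9 = 62.2, rounded up to 63, so the dropout step reproduces exactly. The 56 does not follow from a two-sided paired t calculation, which gives 48. A signed-rank version with the minimum relative efficiency of 0.864 gives 55, but the article does not name a method. This point does not depend on how 56 arose, so it is taken as given.

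**Planned losses:** 63 − 56 = 7. This is a ceiling for the group at issue, because some of the 7 may leave before or after the glove period, or refuse any visit.

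**Planned standard error:** 5.2/√56 = 0.695 kg, reading 5.2 kg as the SD of the change.

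**Shift from leaving out withdrawers.** Let the 56 completers gain 2.16 kg on average. Let k withdrawers be measurable at T3 and T4, with mean change r. The mean including them is (56 × 2.16 + k × r)/(56 + k), so

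shift = (2.16 − r) × k/(56 + k).

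Both r and k are assumptions; the article gives neither.

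| k | r = 0 kg | shift/SE | r = 1.08 kg | shift/SE | r = 2.16 kg |
|---|---|---|---|---|---|
| 2 | 2.16 × 2/58 = 0.07 kg | 0.11 | 1.08 × 2/58 = 0.04 kg | 0.05 | 0 |
| 4 | 2.16 × 4/60 = 0.14 kg | 0.21 | 1.08 × 4/60 = 0.07 kg | 0.10 | 0 |
| 7 | 2.16 × 7/63 = 0.24 kg | 0.35 | 1.08 × 7/63 = 0.12 kg | 0.17 | 0 |

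In the largest case, the mean over all 63 is 1.92 kg instead of 2.16 kg. Outside this range, withdrawers who would lose 1 kg give 3.16 × 7/63 = 0.35 kg, and withdrawers who would gain more than completers reverse the sign.

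**What could still be recovered.** The Results section reports 52 enrolled by October 2021, so 63 − 52 = 11 were still to come. At the planned rate, 11 × 7/63 = 1.2 of them would drop out. One person at r = 0 shifts the mean by 2.16 × 1/57 = 0.04 kg, about 0.05 SE. Anyone then in the glove period adds to this.

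**The case against.** The strongest case against runs as follows.

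- **The rule is for people leaving the study.** Agreeing to a grip test and a 15-minute interview is not agreeing to two full visits. A short request that includes the primary outcome is sensible for someone on the way out. This stands in part: willingness to attend is assumed, and some will refuse. It does not explain why they are not asked.
- **The text does not exclude T3 and T4.** Correct. A reader might infer that the plan bars withdrawers from these visits, but the article only fails to seek them. The interview is normally a T3 item, so the list could be read as a shortened T3. Even so, T4 is not sought, and the analysis set requires both.
- **The timing of the grip test may be in the full protocol.** That is possible, and the missing time alone does not affect the estimate, because the value is not used in it. The point rests on the stated rule combined with the stated analysis set.
- **The direction is not established.** This stands. The Discussion says disappointed participants may leave more often; it says nothing about their unsupported grip change.
- **The authors already name the risk and plan a dropout analysis.** True, but describing dropouts does not recover their outcomes.
- **Asking for T3 and T4 would not be enough.** This stands. The sentence on dropouts could still send someone who left the intervention early, but attended both visits, to the separate analysis. The Statistical Analysis section must change too.

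A reader might also infer that everyone who stops wearing the glove is lost. The article does not support that. Study Design has all participants assessed five times, and Intervention leaves the amount of use to them, so someone who stops the glove without withdrawing is still due at T3 and T4.

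**Conclusion.** The concern holds as a modest design weakness. The withdrawal rule does not seek T3 or T4, and the analysis rule keeps withdrawers' grip values out of the effect estimate. In an uncontrolled trial whose authors foresee dropout linked to disappointment, this may bias the pre-post change, possibly upward.

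The size is 0 to 0.24 kg, at most 0.35 SE. That rests on three assumptions: completers gain the planned 2.16 kg, withdrawers would change by between 0 and 2.16 kg, and no more than 7 people are affected. With 2 to 4 people and a response of zero or half the planned gain, it is 0.05 to 0.21 SE. A reader might conclude that the trial will overstate the benefit; the article does not show this, since it gives no grip outcome for people who leave. The change is optional and inexpensive, and it does not correct a demonstrated error.

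**What to change.** Change both places; either change alone is not enough.

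1. **Withdrawal paragraph (Secondary Outcome Measures).** Ask anyone who leaves the intervention early, but does not refuse measurement, to attend T3 within 1 week of when the 6 weeks would have ended and T4 4 weeks later, at least for handgrip strength. Keep the present reduced set for those who refuse these visits, and record the date of the grip test.
2. **Statistical Analysis.** State that anyone with T3 and T4 handgrip data enters the handgrip effect analysis whatever their glove use, and that dropout means having no T3 and T4 data. This fits a set already defined by attendance.

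**Cost.** "All assessments are estimated to take 1.5 to 2 hours", so two visits take 2 × 1.5 = 3 to 2 × 2 = 4 hours per willing person: 6 to 8 hours in total for 2 people, 21 to 28 for 7, and less if only handgrip is tested. Under the Ethics section, the amendment needs committee approval and then notice to all centers and the monitor.

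**Limit.** The benefit reaches only participants who have not finished. The Results section says "As of March 2022, the study is still ongoing", so some benefit may remain, but by then it may be less than the roughly one person estimated from October 2021 enrolment.
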